### Adverse events management

All adverse events (AE) will be recorded on the OPTIMA Adverse Events Form. The record will include a brief description of the event, any clinical symptoms and a date when the event started and stopped, and who was involved (e.g., a child, a parent, another family member). The researchers will be recording any AE they noted in their communications with the participant at any point during the study. In addition, to adverse events disclosed spontaneously by participants, information about adverse events will be collected online at 2 weeks post-baseline assessment using OPTIMA adverse events questionnaire.

All completed adverse event forms will be reviewed by the research team to identify any Suspected Unexpected Serious Adverse Reaction (SUSAR). If an event meets the definition of a SUSAR (any serious adverse event that is related to the trial intervention and unexpected, i.e., not listed in the protocol as an expected side effect of the intervention) then the member of staff that received the information must inform the Chief Investigator (CI) within 24 h of becoming aware of the serious adverse event and provide all necessary information. Each case will be assessed by the CI, team clinical expert and medical expert for seriousness, expectedness and relatedness to the study. The CI will then take appropriate action, which may include halting the study and informing the Sponsor of such action. Events categorised in the protocol as an expected (see Table 3), do not need to be reported.

**Table 3 Tab3:** Expected adverse events

School & community	Family dynamics	Parental wellbeing
• Increased child refusal to go to school/community activities. • Exclusion from school/community activities.	• Deterioration in child behaviour (including self-harm) or wellbeing. • Deterioration in sibling wellbeing (including self-harm). • Increased family discord. • Breakdown in family structure. • Social work involvement or child protection concerns.	• Increased depressed mood • Increased anxiety/stress • Increased tiredness/fatigue • Increased/decreased sleep

STEPS is a psychological intervention, not pharmacological, and so physical adverse reactions are not expected. Medical adverse events will be recorded using standard medical definitions.

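### A serious event in a Table 3 category, such as self-harm, need not reach the Chief Investigator or the expert assessors, because the duty to inform covers SUSARs only and listed events are exempt whatever their seriousness

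*Protocol article*

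**What the plan says.** All the relevant rules are in the protocol article under Adverse events management.

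- Recording is universal: "All adverse events (AE) will be recorded on the OPTIMA Adverse Events Form".
- The first review has one stated purpose: "All completed adverse event forms will be reviewed by the research team to identify any Suspected Unexpected Serious Adverse Reaction (SUSAR").
- A SUSAR is defined as "any serious adverse event that is related to the trial intervention and unexpected, i.e., not listed in the protocol as an expected side effect".
- If an event meets that definition, "the member of staff that received the information must inform the Chief Investigator (CI) within" 24 hours.
- Expert judgement comes next in the text: "Each case will be assessed by the CI, team clinical expert and medical expert for seriousness, expectedness and relatedness to the study". The CI's power to act, up to halting the study and telling the sponsor, follows from this step.
- The section's text before Table 3 closes with the exemption: "Events categorised in the protocol as an expected (see Table 3), do not need to be reported".

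Table 3, headed as expected adverse events, includes "Deterioration in child behaviour (including self-harm) or wellbeing", "Deterioration in sibling wellbeing (including self-harm"), and social work involvement or child-protection concerns. No entry carries a severity limit.

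**The concern.** Expectedness and seriousness are separate properties of an event. An event can be foreseeable in this population and still be serious in a particular family. The section uses membership of a list to settle what must be passed on, and some entries on that list span a wide range of severity.

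At stake is whether the people given the task of judging seriousness are assured of seeing the events for which that judgement matters most. The CI's response, including a possible halt, is described as following their assessment. An event that need not be assessed need not prompt that response either.

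**Working it through.** No arithmetic on outcomes applies, and the plan gives no figure to reproduce. The check is to follow an event through the stated rules.

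**Inputs, all from Adverse events management**

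- S: the event is serious.
- R: it is related to the intervention.
- L: it falls in a category that the protocol lists as expected. Table 3 is the only such list in the article.
- Duty to inform the CI: applies when the event meets the SUSAR definition, that is, S and R and not L.
- Exemption: applies when L holds, with no condition on S or R.

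**Trace**

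| Event | Recorded, seen by research team | Meets SUSAR definition | Duty to inform CI | Exempt from reporting |
|---|---|---|---|---|
| Serious, related, not listed | Yes | Yes | Yes | No |
| Serious, related, listed | Yes | No, since L holds | No | Yes |
| Not serious, listed | Yes | No | No | Yes |

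The second and third rows have the same outcome. Once L holds, the SUSAR condition fails whatever S and R are, so the stated rules treat a serious and a trivial event in a listed category alike.

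**Size of the list**

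Table 3 has 2 entries under school and community, 5 under family dynamics and 4 under parental wellbeing: 2 + 5 + 4 = 11. Three of the 11 name self-harm (child or sibling) or child-protection concerns. Others, such as tiredness or a change in sleep, are usually mild.

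**Two readings of the assessment sentence**

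1. Each case means each SUSAR notified to the CI. The three assessors then need not see a serious listed event.
2. Each case means every adverse event. The assessors then see all events, but this does not fit a duty to inform the CI that is confined to SUSARs, nor an unconditional exemption.

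The sentences need reconciling on either reading.

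**Is there another route to the CI?**

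- The Adverse events paragraph among the measures describes online collection and refers back to this section.
- Data monitoring describes a Programme Steering Committee that meets six-monthly, with one meeting at the end of the study. No separate monitoring committee is formed unless that committee asks for one.
- Post-study care describes four-weekly emails that give parents contact details for local services.

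None of these requires a serious listed event to be passed to the CI.

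**The case against.** The strongest defence has four parts.

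*The research team sees every form.* This is true, and its composition is not stated. It may include clinicians or the CI. A reader might infer that serious listed events never reach clinical eyes, or that nobody clinical judges seriousness before the exemption applies. The article supports neither. What stands is that the text does not require the named assessors to see such events.

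*Screening followed by expert confirmation is ordinary.* Also true. Staff flag a suspected event and experts then adjudicate it, so it is no fault that staff form a first view on the properties the experts later judge. The difficulty is that listing in Table 3 removes an event from the first stage whatever its seriousness.

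*The exemption may concern external reporting only.* It comes directly after the sentence on informing the sponsor, so this reading is natural. But no recipient is named, and even on this reading the duty to inform the CI still covers SUSARs alone.

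*The article condenses a full protocol (version 5.0) that is not shown.* Seriousness criteria and escalation procedures may well be there, and their absence here is not held against the plan. The point rests on two rules that the article does state: a duty limited to SUSARs and an exemption without a seriousness condition.

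Two further inferences are tempting but unsupported. One is that the Steering Committee would see no signal. All events are recorded, the committee oversees the study, and nothing says records are withheld from it. The other is that the later trial would inherit the procedure. What is piloted is adverse event collection, which Table 1 measures by questionnaire completion within 7 days and the number of reminders. No protocol for the later trial is shown.

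**Conclusion.** The concern holds as a conflict and gap in the stated reporting rules. Followed as written, they allow a serious event in any of 11 listed categories to be recorded and reviewed by the research team without any requirement that it reach the CI, clinical expert and medical expert. Three of those categories name self-harm or child-protection concerns.

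This rests on two assumptions: that the list in the SUSAR definition is Table 3, and that the full protocol does not override the article's wording. The documents give no rate for such events among up to 100 families followed for 4 weeks, so no expected number is offered. The finding does not show that any event was missed. It is worth correcting because it concerns participant safety and the remedy is cheap.

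**What to change.** Reconcile three statements in Adverse events management: the SUSAR-only duty to inform the CI, the assignment of each case to the three assessors, and the Table 3 exemption. The reconciled text should make two things clear.

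1. Listing in Table 3 does not by itself bypass the assessment of seriousness by the assessors already named. It should also say which events the phrase about each case covers.
2. To whom the exemption applies, for example external reporting only.

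Which clinical reporting rule to adopt is for the investigators and sponsor to decide. The cost is a change of wording and a few more events for the existing assessors to look at, with no new staff or data collection. The article states that recruitment is complete, so for this study the practical step is to check that recorded Table 3 events were assessed for seriousness. The wording should also be settled before any of it is reused.

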### Ethics

The application for ethical approval for the study was submitted to the London-Riverside Research Ethics Committee (REC) and received a favourable opinion on further information on 17 November 2020, REC reference number: 20/LO/1173.

To allow maximum flexibility in terms of recruitment, a substantial amendment to the ethical application was submitted to the REC in March 2021. This amendment introduced two additional methods of participant identification (Method 2: ICAN and Method 3: a manual review of referral lists). This amendment was approved in April 2021. The REC was notified of two further non-substantial amendments, which did not require study-wide review, one in May 2021 and the second one in June 2021. The current manuscript is based on protocol version 5.0 dated 10 June 2021.

Recruitment for the study commenced in April 2021 and will continue until the end of July 2021.

### Protocol amendments

In case of new information becoming available, which may result in significant changes to the risks and benefits of taking part, the Participant Information Sheet and informed consent form will be reviewed and updated accordingly. All participants actively enrolled in the study will be informed of the updated information and will be given a revised copy of the Participant Information Sheet and informed consent form to confirm their wish to continue taking part.

### Consent

#### Parents

All participants will provide written informed consent to take part in the feasibility study. The informed consent form will be provided in electronic form using Qualtrics to be completed by the participant before they enter the study. The researcher will explain the details of the study, provide the Participant Information Sheet and will answer any questions that the participant has concerning the study. They will also inform parents that participation is completely voluntary, and they are under no obligation to take part and they can withdraw at any time without their care being affected. The researcher will also tactfully check whether it is a convenient time for a parent to commit to the study (i.e., if there is no expected imminent change to their existing care commitments, for example, late stage of pregnancy). On the consent form, there will be a separate statement requesting permission to contact the child’s teacher. If this box is not ticked, the teacher will not be contacted. If parents are unable to understand the consenting process it will be assumed that they do not meet the language requirement for the study.

#### Teachers

Parents, who have given consent to contact their child’s teacher, will be asked to provide the name of their child’s school and the teacher’s name. The research team will then contact the teacher (by phoning or emailing a school) and invite them to take part in the study. An invitation will be followed up with an email containing a link to the teacher survey. This survey will include Teacher Information Sheet, a consent statement and a questionnaire. Teachers will also be invited to contact the research team with any questions that they might have about the study before they agree to take part.

### Confidentiality

The CI and all members of the research team will take every effort to preserve the confidentiality of participants taking part in the study. To de-identify the data, each participant will be assigned a study ID. Participants identifiable data required for administrative purposes (e.g., name and contact details) will be stored in a separate, encrypted, password-protected file. These will be accessed only by those members of the research team who are responsible for contacting participants (e.g., to email a link to the online survey). No individual participant’s data will be identifiable in the publications or reports that may result from this study.

### Post-study care

Participants will continue to have access to the STEPS app for 9 weeks after the study ends. This means that overall, participants will have access to the intervention for 12 weeks.

During this time, the researchers will check in with each participant every 4 weeks (by email) and provide contact details for the local clinical services in case a parent/caregiver has any major concerns about themselves or their child. The check-in email will also remind the participant when their app access is due to expire.

## Discussion

The long waiting lists to receive assessment and treatment from children’s mental health and paediatric or early behavioural help services mean that parents can be left without support and guidance at the time when it is most needed. Furthermore, anecdotal evidence suggests that due to the COVID-19 pandemic-related disruptions, families wait for support longer than ever before. Given that over 80% of adults in the UK own a smartphone, the use of a digital application to deliver support and training to parents on the waiting list could provide a clinically effective and low-cost solution to support families when in-person clinical support is not available. The planned RCT will seek evidence whether the STEPS app is a clinically and cost-effective intervention for parents of hyperactivity/impulsivity and inattention children with challenging behaviour during the time they remain on the waiting list for assessment.

However, recruiting from the waiting list is challenging. First, the traditional methods, for example, clinician referral, are not feasible due to the very limited contact between the clinician and the family during that time. Second, obtaining consent for research contact that would allow the researchers to get in touch with the family and invite them to participate in the study is also limited, as this is typically discussed during the assessment visit. Moreover, while the number of health research studies that adapted to remote consenting and data collection procedures has rapidly increased in recent months due to the COVID-19 pandemic-related restrictions on in-person contact, the evidence showing that participation in remote health studies is acceptable is lacking. This is especially important in the context of conducting research with parents, who are often more difficult to reach and engage due to a complex set of challenges in the families (e.g., parental ADHD or mental health concerns).

To ensure the timely and efficient evaluation of STEPS in OPTIMA, we have worked with children’s services to implement a remote strategy for recruitment, screening and assessment of recently referred families—part of which is incorporated into routine clinical practice and part of which is OPTIMA specific. The purpose of this study is to establish whether we can use this approach to recruit an adequate number of participants to run a randomised controlled trial and to measure whether obtaining consent and collecting data from parents and teachers using remote methods (online and on the phone) is acceptable to the study participants. We will use three different methods of identifying participants: this will include the new digital platforms that allow to obtain screening information and collect consent for research contact, as well as traditional manual methods of recruitment. This will maximise the opportunities for recruitment by involving a wide range of health services. Although the originally approved study protocol included only one option of identifying participants (through MHE; see Method 1: myHealthE portal), our discussions with the services that were interested in joining as recruitment sites revealed that it was not always possible to adopt digital platforms. In response to this, a substantial protocol amendment was submitted for ethical review to allow other methods of participant identification. It is also possible that other sites may not have the capacity to support manual recruitment and adopting digital methods may be the only viable option. Adopting a range of approaches to identifying participants, will also allow us to establish which of the methods is most effective when recruiting from the waiting list and inform the approach. Therefore, the results from this study may provide valuable information for other researchers planning to recruit a substantial number of participants from the waiting list.

Finally, for practical as well as scientific reasons, the present study, as well as the future RCT of STEPS, will necessarily have to focus on parents with an adequate level of English who have access to a smartphone. However, it is important to acknowledge that these eligibility criteria may reduce participation opportunities for parents from ethnic minorities or from more deprived areas. We plan to work with OPTIMA Patient and Public Involvement Panel, as well as with the newly launched NIHR Maudsley Biomedical Research Centre Race and Ethnicity Advisory group on identifying feasible solutions that could help reduce the barriers for inclusion.

### Study status

At the time of manuscript submission, the study was open to recruitment. Recruitment has now been completed.

## Data Availability

Not applicable.

## Abbreviations

ADHD: Attention-deficit/hyperactivity disorder
AE: Adverse event
CAMHS: Child & Adolescent Mental Health Services
CI: Chief investigator
DMC: Data Monitoring Committee
ICAN: Interactive CAMHS Assessment Network
ICF: Informed consent form
MHE: MyHealthE
ODD: Oppositional defiant disorder
RCT: Randomised controlled trial
REC: Research Ethics Committee
SUSAR: Suspected Unexpected Serious Adverse Reaction
SDQ: Strengths and Difficulties Questionnaire
STEPS: Structured E-Parenting Support
PSC: Programme Steering Committee
